**Fig. 1 Fig1:**
[figure not shown]
Study design flow of DiaSmokeFree; *V* visit, *C-F NA* combustion-free nicotine alternatives

Participants will attend a screening visit within 28 days prior to study visit 1 (Tables 1 and 2). During the screening visit, socio-demographic data, detailed medical history (including medication use), and detailed history of smoking, vaping, and heated tobacco products (HTPs) use will be collected. Additionally, participants’ intention to quit smoking will be assessed. All patients will be offered a smoking cessation program according to the local guidelines. A second opportunity to enroll in a free smoking cessation program will be offered before study enrollment. Any participant who expresses the intention of booking for the cessation program or to quit smoking in the next 6 months will be urged to do so and not be recruited in the study. Patients taking part in the study will be informed that they are free to quit smoking and withdraw from the study at any time. Moreover, participants will be encouraged to quit smoking at every contact time point throughout the whole study.

**Table 1 Tab1:** Study assessments (Control group—Arm A)

Procedure	Screen (V0)	Baseline (V1) day 1	Week 12 (V2) day 90 ± 5	Week 24 (V3) day 180 ± 7	Week 52 (V4) day 360 ± 7	Week1 04 (V5) day 720 ± 7
Eligibility criteria check	X	X				
Medical Hx	X					
Medication use		X	X	X	X	X
Smoking/vaping Hx	X					
Cigarette consumption	X	X	X	X	X	X
Exhaled CO		X	X	X	X	X
FTND		X				
Intention to quit	X	X				
Informed consent		X				
Randomization		X				
Tracker APP installation		X				
Vital signs		X	X	X	X	X
Weight, BMI, waist circumference		X	X	X	X	X
Body composition equation*		X	X	X	X	X
QoL questionnaire		X	X	X	X	X
Smoking cessation advice	X	X	X	X	X	X
Spirometry		X				X
Metabolic syndrome assessment**		X	X	X	X	X
Blood sample***		X	X	X	X	X
Testosterone (men only)		X	X	X	X	X
Urine albumin to creatinine ratio (ACR)						
Safety reporting		X	X	X	X	X

*BL* baseline, *V* visit, *Hx* history, *CO* carbon monoxide, *BMI* body mass index, *FTND* Fagerstrom Test for Nicotine Dependence, *QoL* quality of life, *CBC* complete blood count, *WBC* white blood cells, *Hb* hemoglobin, *LDL* low-density lipoprotein, *HDL* high-density lipoprotein, *HbA1*_*C*_ glycated hemoglobin, *AE/SAE* (serious) adverse incidents

*Body composition (fat and skeletal muscle mass) by validated equation by Lean ME et al. (1996) and Al-Gindan YY et al. (2014)

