After randomization, participants’ smartphones will be equipped with a dedicated tracker application. This application is designed to monitor individual behaviors such as physical activity, adherence to capillary blood glucose monitoring, cigarette smoking frequency and daily C-F NA usage. The tracker application will also identify any protocol violations, collect adverse events and send reminders (e.g., next scheduled appointment, study restrictions, instructions) throughout the study duration. The use of a dedicated tracker application adds an innovative element to continuously collect data and enhances adherence to the study protocol.

After the baseline assessments (Visit 1), participants will be invited to attend four more clinical visits (Visits 2–5), which will be conducted in an ambulatory (outpatient) setting. During these visits, a number of measurements will be taken, with a particular focus on metabolic syndrome parameters, i.e., waist circumference, systolic blood pressure value, venous blood concentration of triglycerides, HDL, and fasting blood glucose (Tables 1 and 2). Also, two questionnaires will be used.

(Diabetes Quality of Life questionnaire and the Fagerström Test for Nicotine Dependence) to assess specific aspects of participants' health and smoking behavior.

Following each clinical visit, participants will be provided with an appropriate number of consumables (cartridges/pods or e-liquids refill bottles for e-cigarettes, tobacco sticks for HTPs) if they are in the intervention arm (Arm B). Participants in the intervention arm will have additional non-clinical visits between the clinical visits. These non-clinical visits are designed to replace any used consumables and provide an opportunity for study investigators to stimulate retention and check compliance. At these non-clinical visits, participants in Arm B will be required to return all empty, part-used, and unused consumables from the previous study period. This evaluation of the habitual pattern of C-F NA use and verification of product adherence are essential for monitoring the participants' compliance with the intervention.

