Before each study visit, participants will be required to fast overnight (from midnight). During the clinic visits, clinical laboratory evaluations will be performed on fasting blood samples. Participants will also receive instructions to refrain from consuming alcohol for 24 h prior to clinic visits and will be advised not to consume more than 14 units of alcohol per week throughout the entire study duration. This is to minimize any potential interference of alcohol consumption with study outcomes and to maintain consistency in data collection. Throughout the study, any modifications in participants' diet and/or anti-diabetic medication will be regularly recorded and monitored.

At each visit, all participants will be advised and encouraged to completely quit smoking. They will be explicitly informed about the risks associated with smoking and will be offered referral to free smoking cessation programs at every contact time point.

Premature withdrawal from the study may occur if a participant experiences a severe adverse event (SAE), sustains any uncorrectable protocol deviations during the study, exhibits uncooperative behavior or non-attendance, decides to stop their participation at any time, becomes pregnant, or decides to accept the investigators advice to completely stop smoking.

The DiaSmokeFree study is designed as an unblinded trial due to the nature of the intervention, where participants and trial staff cannot be blinded to the specific intervention being provided (either C-F NA or brief smoking cessation counseling).

To ensure the integrity and reliability of the study data, the source data and source documents will be managed according to Good Clinical Practice (GCP) guidelines. The trial will formally conclude on the date of the last visit of the last patient in the last country participating in the trial.

For data collection, each individual patient will be allocated an electronic case report form (eCRF). Anonymized data from each study visit will be entered directly onto the eCRF, which will then serve as a source document for the trial. This data entry process ensures that data is collected accurately and consistently at all study sites. To maintain data quality, the study will use standardized instruments, such as the Diabetes Quality of Life questionnaire and the Fagerström Test for Nicotine Dependence, to assess specific aspects of participants' health and smoking behavior.

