### Statistical considerations

#### Powering and sample size calculation

The sample size calculation is based on assumptions that the expected reduction in MetS prevalence after smoking cessation is 15% [24–28], and the expected baseline prevalence of MetS in T2D is 70% [29–32]. Sample size was calculated on the basis of demonstration of superiority, assuming a normal distribution of the sample [33]. Significance level was set at 5% (*α* = 0.05), with a power of 80% (*β* = 0.20). Based on these assumptions, the minimum number of subjects with analyzable data required is 160 per treatment arm (N). Considering an estimated 50% proportion of subjects in the intervention arm achieving sustained reduction in cigarette consumption of at least 80% for the study duration [34–38], the final number of subjects required in the intervention arm (N2) is set at 320. Taking into consideration the expected 20% withdrawal rate in both arms over 2 years, the total number of subjects recruited in each treatment arm is increased by this amount. Thus, the total number of subjects for both arms is set at 576.

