#### Statistical analyses

The primary end point for the statistical analysis will be the between-groups difference in the calculated prevalence of MetS after at least 24 months of follow-up. The full analysis set (FAS) will include all subjects randomized to the intervention arm who achieve a sustained reduction in cigarette consumption of at least 80% during the follow-up, combined with all subjects randomized into the usual standard of care control group. Two approaches to the primary analysis will be used: (a) unadjusted analysis, based on a direct comparison of the change in prevalence using a Z test, and (b) adjusted analysis, where potential confounders (including age, gender, smoking, and medications for hypertension, hyperlipidemia, or diabetes) will be analyzed to identify factors that may influence the primary outcome. A generalized linear model will be used to adjust for identified confounders. Any difference between the groups will be assessed for statistical significance at a two-sided alpha of 0.05.

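### Participants who stop smoking may be withdrawn from the study, so control quitters can lack a 24-month MetS value, and the position of full switchers in Arm B is left open

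*Protocol article*

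**What the plan says.** All references are to the protocol article.

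- **Withdrawal (Study design).** One listed ground for leaving early is that the participant "decides to accept the investigators advice to completely stop smoking". The lead-in is permissive: withdrawal may occur. It names no arm, and it speaks of the study, not of the study product.
- **Advice to quit (Study design, Tables 1 and 2).** The same section says: "At each visit, all participants will be advised and encouraged to completely quit smoking". Participants are also told that "they are free to quit smoking and withdraw from the study at any time". Cessation advice is scheduled at 4 post-baseline visits in Arm A and 17 in Arm B, because "Participants in the intervention arm will have additional non-clinical visits between the clinical visits".
- **Assumed effect (Powering and sample size calculation).** The article states that "the expected reduction in MetS prevalence after smoking cessation is 15"%, from a baseline prevalence of 70%. Objectives and end points makes clear that this is an absolute reduction.
- **Analysis (Statistical analyses).** The primary comparison is "the between-groups difference in the calculated prevalence of MetS after at least 24 months of follow-up". The full analysis set takes every randomised control, and from Arm B those whose cigarette use stays down by 80% or more.
- **Compliance (Discussion).** Replacing cigarettes wholly or mostly with the study product is treated as what the trial needs in order to see its effect.
- **After discontinuation (Data monitoring and study safety).** The only follow-up described is for adverse events.

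**The concern.** The rule ties loss of follow-up to a change in smoking, which is the exposure the trial studies. The plan itself assumes that stopping smoking lowers MetS prevalence by 15 points, so 24-month values missing for this reason are informative about the outcome.

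In Arm A, quitting is what the standard-of-care counselling aims at. If those who quit leave the study, the controls with a 24-month value are mainly persisting smokers, although the analysis set is defined as all randomised controls. Observed control prevalence then tends to sit above the prevalence in the whole control arm, which enlarges the difference in favour of the intervention.

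In Arm B the question is whether someone who gives up cigarettes entirely by switching has completely stopped smoking. The withdrawal list does not say. If the answer is yes, the most complete responders may be lost. If it is no, a participant can become cigarette-free and stay in the study in Arm B, but by quitting may be withdrawn in Arm A.

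**Working it through.** **1. The plan's own sample size.** Inputs from Powering and sample size calculation: 70% against 55%, alpha 0.05 (two-sided, from Statistical analyses), power 80%.

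n = (1.960 + 0.842)² × (0.70×0.30 + 0.55×0.45) / 0.15² = 7.85 × 0.4575 / 0.0225 = 159.6, so 160 per arm. Doubling Arm B and multiplying by 1.2 gives 192 + 384 = 576. Both stated figures reproduce and are not in dispute here.

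**2. Control arm, illustration.** Let q be the share of controls who quit, and suppose all of them are withdrawn. The documents give no q, so 5%, 10% and 20% are assumed. MetS prevalence is taken as 70% in the other controls and 55% in quitters, which applies the plan's own cessation effect.

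- Prevalence with everyone followed = (1 − q) × 70 + q × 55
- Prevalence observed with quitters gone = 70
- Overstatement of the difference = 15 × q points

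| q | all followed | observed | overstatement |
|---|---|---|---|
| 5% | 69.25% | 70% | 0.75 points |
| 10% | 68.5% | 70% | 1.5 points |
| 20% | 67.0% | 70% | 3.0 points |

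Against the planned 15 points these are one twentieth, one tenth and one fifth. They are smaller if only some quitters are withdrawn, or if quitting changes MetS by less than 15 points. The sign itself depends on quitters having the lower prevalence.

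**3. Arm B numbers.** After 20% withdrawal, 192 × 0.8 = 153.6 controls remain, and 384 × 0.8 × 0.5 = 153.6 Arm B responders. Unpooled power for 15 points is Φ(0.15/√(0.4575/153.6) − 1.96) = Φ(2.75 − 1.96) = 78.5%.

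Suppose, purely as an assumption, that a further 30% of these responders were withdrawn as full quitters. Then 107.5 remain, the standard error is √(0.21/153.6 + 0.2475/107.5) = 0.0606, and power is Φ(2.48 − 1.96) = about 70%. Total Arm B withdrawal would be (76.8 + 46.1)/384 = 32%, against the 20% the plan allows.

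**4. Can the planned analyses repair it?** The Z test compares observed prevalences. The generalized linear model adjusts for covariates such as age, smoking and medication. Neither supplies an outcome that was never measured. Imputing quitters' values from controls who went on smoking would carry the same upward error as step 2.

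**The case against.** Several points on the other side have force.

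- **The rule is permissive and quitters may be few.** Withdrawal may occur; it need not. The trial enrols only people who refuse cessation programmes and excludes anyone who wants to quit within 6 months. This limits the likely size. It does not remove the mechanism, and discretion in an open-label trial can add selection of its own.
- **Being free to quit and to withdraw may be two separate freedoms.** That is a fair reading of the sentence told to participants. The withdrawal list is not open to it: there, deciding to stop smoking is itself a ground.
- **Full switchers are probably meant to stay.** The 80% threshold includes 100%, the full analysis set admits those who meet it, and the Discussion wants cigarettes replaced wholly or mostly. This stands. Loss of Arm B's best responders cannot be asserted as what the plan prescribes, only as something its wording leaves open.
- **Control quitters remain in the analysis set, and an unseen analysis plan may handle missing values.** True as far as it goes. But an analysis plan cannot create visits that were not held, and nothing shown says they are held.
- **The 20% allowance covers it.** It covers numbers, not bias. It does, however, undercut the 70% power figure in step 3, which adds an assumed 30% loss on top of the allowance and keeps the effect at 15 points after removing those assumed to benefit most.
- **The intended comparator is people who go on smoking (Discussion).** Statistical analyses says all randomised controls. Choosing controls by behaviour after randomisation would give up the balance the Discussion claims from randomisation.

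**Conclusion.** The point holds for the control arm. Applied as written, the rule leaves control quitters without a 24-month MetS value, in conflict with an analysis set of all randomised controls, and the planned analyses cannot recover those values. The likely direction favours the intervention. The overstatement is 0.15 points for each 1% of controls who quit and are withdrawn, given 70% and 55% MetS prevalence; the quit rates are assumptions.

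For Arm B the finding is an ambiguity that must be resolved. If full switchers are withdrawn, analysable responders are lost, but the document does not allow the size to be computed.

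A reader might infer more, and the documents do not support it:

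- that the rule certainly removes the best responders in Arm B, or cuts power to about 70%;
- that losses are known to differ between the arms. The 17 against 4 advice contacts make this plausible, but the plan assumes 20% in both, and the net bias cannot be derived;
- that the trial discards its own outcome. Quitting is exposure; the outcome is MetS;
- that the other withdrawal grounds, such as protocol deviations or uncooperative behaviour, should be struck out too. Nothing here examines their effect.

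**What to change.** Reconcile the withdrawal list and participant information in Study design with the analysis set in Statistical analyses and the compliance aim in the Discussion:

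1. State that stopping smoking is not in itself a reason to end follow-up.
2. Separate discontinuing the study product, which applies to Arm B only, from withdrawing consent to follow-up, which applies to both arms.
3. Collect the MetS assessments scheduled at Visits 2 to 5 on every randomised participant who still consents, quitters included.
4. Analyse control quitters in their assigned arm.
5. State that Arm B participants who switch completely remain in the study.

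This concerns data collection and analysis only; advice, referral and clinical decisions are untouched.

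The cost is an amendment, ethics approval at the sites (seven committees approved the study) and revised participant information, since participants are now told that they may quit and withdraw. No visits are added. Assessments missed before the change cannot be recovered, so it gains most if made early.

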### Patient and public involvement

In the DiaSmokeFree study, patient and public involvement consisted of a focus group of smokers with T2D. The focus group feedback was used to shape and refine the trial design, ensuring that the study is more relevant and responsive to the needs and expectations of its target population. Moreover, the study protocol has been reviewed by the Research and Development (R&D) Committee of Ashford and St Peter’s Hospitals NHS Foundation Trust, which includes a patient representative, thus ensuring that the study is ethically sound, aligns with patient interests, and respects patient rights. By involving patients and the public in the study design and review process, the DiaSmokeFree study demonstrates a commitment to patient-centered research.

### Objectives and end points

Primary end points: The primary objective of the study is to assess the impact of sustained use of C-F NA on the proportion of patients with metabolic syndrome (MetS) among individuals with T2D. The MetS will be defined by the National Cholesterol Education Program (NCEP) MetS score [23], and the primary end point will be the change in the prevalence of an NCEP MetS score below the diagnostic threshold (< 3) between baseline and the 2-year follow-up. The comparison will be made between patients with T2D in both arms of the study.

Secondary end points: The study will also assess the change in MetS prevalence at 3 months, 6 months, and 1 year as secondary outcomes. All assessments at each time point will be performed in all participants in both arms of the study.

Considering the results of several lifestyle modification interventions, the absolute reduction in MetS prevalence after smoking cessation is expected to be no less than 15% [24–28].

Additionally, the study will analyze the absolute change in the sum of the individual factors of MetS, as defined by NCEP criteria, at each study time point (between and within study groups. Other secondary end points will include changes in each individual factor of MetS and changes in the variables at each study time point (between and within study groups).

### Statistical considerations

#### Powering and sample size calculation

The sample size calculation is based on assumptions that the expected reduction in MetS prevalence after smoking cessation is 15% [24–28], and the expected baseline prevalence of MetS in T2D is 70% [29–32]. Sample size was calculated on the basis of demonstration of superiority, assuming a normal distribution of the sample [33]. Significance level was set at 5% (*α* = 0.05), with a power of 80% (*β* = 0.20). Based on these assumptions, the minimum number of subjects with analyzable data required is 160 per treatment arm (N). Considering an estimated 50% proportion of subjects in the intervention arm achieving sustained reduction in cigarette consumption of at least 80% for the study duration [34–38], the final number of subjects required in the intervention arm (N2) is set at 320. Taking into consideration the expected 20% withdrawal rate in both arms over 2 years, the total number of subjects recruited in each treatment arm is increased by this amount. Thus, the total number of subjects for both arms is set at 576.

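### The 20% withdrawal allowance multiplies by 1.2 instead of dividing by 0.8, so 576 patients leave about 154 per compared group, below the plan's own minimum of 160

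*Protocol article*

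**What the plan says.** The section *Powering and sample size calculation* of the protocol article builds the total in three steps.

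1. For a fall in metabolic syndrome prevalence of 15 points from 70%, at 5% significance and 80% power, "the minimum number of subjects with analyzable data required is 160 per treatment arm".
2. Half of the intervention arm is expected to sustain a reduction in cigarette consumption of at least 80%, so that arm is set at 320.
3. Withdrawal of 20% over two years is expected in both arms. To cover it, "the total number of subjects recruited in each treatment arm is increased by this amount", and so "the total number of subjects for both arms is set at 576".

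The section *Study design* gives the allocation as 1:2, control to intervention. The section *Statistical analyses* compares all controls with only those intervention patients who sustain the reduction, and states that differences will be "assessed for statistical significance at a two-sided alpha of 0.05".

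**The concern.** The allowance exists so that 160 analysable patients per group remain after withdrawals. If a fraction d of those recruited is lost, n patients remain only when n/(1 − d) are recruited. Adding 20% to n is not enough, because the 20% is later lost from the larger, inflated number. The wording and the total of 576 both suggest that the arms were simply increased by 20%. If so, the stated minimum and the stated 80% power are not met on the plan's own assumptions. There is also no cushion elsewhere. The 160 is the formula's result rounded up by less than one patient, and the oversampling for non-compliance mentioned in the Discussion is already used up in the step from 160 to 320.

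**Working it through.** **Inputs, all from the protocol article**
- Control prevalence 70%; minimum analysable 160 per group; power 80%; responder share 50%; withdrawal 20% in both arms; total 576 (section *Powering and sample size calculation*).
- Reduction of 15 points, described as absolute: "the absolute reduction in MetS prevalence after smoking cessation is expected to be no less than 15" per cent (section *Objectives and end points*). The comparison is therefore 70% versus 55%.
- Two-sided alpha of 0.05 (section *Statistical analyses*).
- Allocation 1:2 (section *Study design*).

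**Step 1: reproduce the 160.** The unpooled normal formula is

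n = [p1(1 − p1) + p2(1 − p2)] × (z₀.₉₇₅ + z₀.₈₀)² / (p1 − p2)²

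= (0.70 × 0.30 + 0.55 × 0.45) × (1.960 + 0.842)² / 0.15² = 0.4575 × 7.849 / 0.0225 = 159.6, so 160.

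This matches exactly. The pooled version gives 163. A one-sided test (126 unpooled, 128 pooled), a continuity correction (176) or a relative 15% reduction to 59.5% (324) does not match.

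**Step 2: reproduce the 320.** 160 / 0.50 = 320. The subtotal is 160 + 320 = 480.

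**Step 3: reproduce the 576.**

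| Allowance | Control | Intervention | Total |
|---|---|---|---|
| n × 1.2 | 192 | 384 | 576 (as stated) |
| n / 0.8 | 200 | 400 | 600 |

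Only multiplication by 1.2 gives the stated total.

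**Step 4: what 576 leaves after 20% withdrawal.**
- Controls: 192 × 0.8 = 153.6.
- Intervention: 384 × 0.8 = 307.2, of whom 307.2 × 0.5 = 153.6 are expected responders.
- Shortfall: 160 − 153.6 = 6.4 per compared group (4%).
- Withdrawal that 192 and 384 do cover: 1 − 1/1.2 = 16.7%.

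**Step 5: power for 70% versus 55%, two-sided 0.05.**

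Unpooled: standard error = √(0.4575/153.6) = 0.05458; 0.15/0.05458 − 1.960 = 0.789; power 78.5%.

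Pooled: standard error under the null = √(2 × 0.625 × 0.375/153.6) = 0.05524; (0.15 − 1.960 × 0.05524)/0.05458 = 0.765; power 77.8%.

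| Analysable per group | Unpooled | Pooled |
|---|---|---|
| 160 | 80.1% | 79.4% |
| 153.6 | 78.5% | 77.8% |

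The withdrawal step costs 1.6 points (unpooled) or 1.7 points after rounding (pooled). The rest of the gap between 77.8% and 80% comes from the choice of pooled over unpooled formula, not from this error.

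**Step 6: check of the remedy.** 200 × 0.8 = 160 controls. 400 × 0.8 × 0.5 = 160 responders. With 600 randomised, the stated minimum is met exactly.

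**The case against.** The best counter-argument concerns the 50%. It is defined as the share of the intervention arm that sustains the reduction for the whole study. A patient who withdraws cannot be shown to have done so, and the 50% may therefore already count withdrawals as failures. There would then be 384 × 0.5 = 192 responders against 153.6 controls, and power would be 82.9% (unpooled) or 81.8% (pooled), above 80%. This is a fair reading of the definition taken alone. It does not fit the calculation, which applies the 20% to both arms after the 50% step and so treats the two as separate losses. It also leaves the control arm, to which the 50% never applies, at 153.6. The control shortfall is therefore firm on either reading, while the loss of power depends on the sequential one that the section itself follows.

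A second argument is that the analysis set names all randomised controls, so all 192 might be analysed. But the minimum of 160 is defined by analysable data, and the allowance is there to protect it. If every control were analysable, no allowance would be needed in that arm.

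Third, the effect is small, and both the 20% and the 50% are planning guesses whose own error could easily outweigh it. That is true. It limits the weight of the point but does not make the stated figures agree.

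**Conclusion.** The concern holds. The total of 576 comes from multiplying by 1.2, and at the plan's own 20% withdrawal it leaves 153.6 per compared group against a stated minimum of 160. The trial is 24 patients short of the 600 that its assumptions require (4%), and power is about 78% instead of 80%. Put the other way, 576 absorbs 16.7% withdrawal, not 20%.

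This rests on 70% versus 55%, a two-sided 5% test, and the 50% responder share applying to patients who remain in the study, as the order of the steps implies. It also takes the comparison of responders with all controls as the plan defines it; whether that is the right comparison is a separate matter. The point should be corrected because the trial relies on these figures and its Conclusions describe it as adequately powered. It does not threaten the design.

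**What to change.** Correct the end of the sample size section in one of three ways.

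- **Restate the power.** For example: 576 randomised gives, after 20% withdrawal, about 154 controls and 307 intervention patients (about 154 expected responders), and about 78% power for 70% versus 55%.
- **Restate the withdrawal covered.** Say that 576 preserves 160 and 320 at a withdrawal rate of up to 16.7%.
- **Raise the total.** If 80% power at 20% withdrawal is to remain the claim, the number is 600 (200 + 400).

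Either of the first two costs one sentence. They leave the abstract unchanged, since it gives the total and the ratio but no power or withdrawal rate. The third means 24 more patients and a changed total wherever 576 appears. As the article expects enrolment to finish by December 2023, restating is the proportionate choice if recruitment has closed. The text should also say whether the 50% is a share of all randomised patients or of those who remain, because the power figure depends on it.
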